### Emotion Regulation

Emotion regulation refers to the way individuals attempt to influence emotions and includes the upregulation and downregulation of positive and negative emotions in accordance with regulatory goals [33]. Emotion regulation and specifically the fostering of flexible use of different emotion-regulation strategies are important topics in the treatment of mental health disorders and more specifically in psychotherapy research. This is made evident by the large number of publications that focus on the topic of emotion regulation [34-37]. Interestingly, emotion regulation has been discussed as a transdiagnostic factor related to psychopathology and the treatment of mental health disorders [34,38-40]. More recently, several mental health interventions that address or target emotion regulation have been developed as web- or mobile-based programs. For example, Böhme and Berking [41] describe the application of an emotion regulation app based on Affect Regulation Training.

By using the extended process model of emotion regulation as a theoretical framework to structure an emotion-regulation intervention [42], Bielinski et al [43] developed REMOTION. The web-based program aims to reduce the symptom severity of patients with a range of different diagnoses while improving their emotion regulation [43]. REMOTION is currently being examined as a blended intervention in an outpatient psychotherapy setting in a pilot randomized controlled trial [43]. It is also currently being examined as an add-on to acute inpatient psychiatric care in another pilot randomized controlled trial (ClinicalTrials.gov NCT04990674). Results for both trials are expected in 2023.

### Aims

Web-based interventions have been efficient and helpful in considering different mental disorders and in self-selected samples in many controlled studies [7]. Nevertheless, little is known about the efficacy of web-based interventions in routine psychotherapeutic practice and their usefulness as an add-on to conventional psychotherapy (BT).

The *first goal* of this study is to assess the effectiveness of 2 web-based interventions (Res-Up! and REMOTION) in an outpatient psychotherapeutic routine setting in comparison with CAU.

The *second goal* of this study is to explore, in a web-based therapy context, the implementation of interventions with either a CAP or COMP focus by using 2 transdiagnostic web-based intervention programs, centered either on activating resilience (CAP; “Res-Up!”) or on emotion regulation (COMP; “REMOTION”).

Further subanalyses considering differences in patients’ benefits depending on their diagnoses will be conducted. In addition, the differential effects of initial resilience and emotion-regulation competencies on the effectiveness of Res-Up! and REMOTION will be explored. To accomplish this, the initial status of resilience and emotion-regulation competencies will be assessed and related to intervention effects in the intervention groups.

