As discussed above, capitalization and compensation can be conceptualized as features of interventions. Another possible conceptualization is via the interaction of intervention focus with patient variables. If particularly patients with a high level of adaptive emotion-regulation strategies profit from an intervention focusing on the improvement of emotion-regulation strategies, this would point toward a capitalization change process. If patients with a low level of adaptive emotion-regulation strategies profit particularly from an intervention focusing on the improvement of emotion-regulation strategies, this points to a compensation change process. Thus, in this trial, differential effects of patients’ initial resilience (respectively emotion-regulation competencies) on the outcome of a resilience and emotion-regulation intervention will also be explored.

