## Methods

### Study Design

The study is a multicenter 3-arm randomized controlled trial in which a CAU approach will be compared with 2 different web-based intervention programs (CAP: Res-Up! and COMP: REMOTION), which will be administered as an add-on to CAU.

Participants in the intervention groups will be given access to Res-Up! and REMOTION immediately, whereas participants in the CAU group will receive access to one of the interventions after 12 weeks (participants in the CAU group can choose which intervention they want to access). Assessments will be made at baseline, 6 weeks (post), and 12 weeks (follow-up) for all participants. Assessments at 6 and 12 weeks will be made irrespective of whether the participant is in face-to-face treatment.

The multicenter trial will take place at the outpatient clinics of the Training Center for Psychological Psychotherapy OWL (Bielefeld, Germany), the Centers for Psychotherapy Dortmund and Muenster (all German Association of Behavioral Therapy—Deutsche Gesellschaft für Verhaltenstherapie [DGVT]), and the Center for Mental Health and Psychotherapy (Department of Psychology and Psychotherapy, University Witten/Herdecke).

Primary and secondary outcomes will be gathered via link to web-based self-report questionnaires based on Qualtrics software [44] at baseline and 6 and 12 weeks after baseline.

All participants will be required to give their informed consent before enrollment in the study. The written consent will be obtained by trained psychotherapists at the outpatient centers. Furthermore, all participants are given the option to contact a study member during the intervention (“guidance on demand”) either via email (REMOTION) or chat (Res-Up!) but are not actively contacted by the team (except for reminders to complete the interventions or questionnaires and a welcome message). Figure 1 displays the flow of patients through the study.

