### Sample Size Calculation

Sample size was calculated with the software G*Power [45]. We aim to detect small effect sizes of Cohen *d*=0.20 regarding the Time×Group interaction for the 2 active conditions at an error level of .05. A power analysis revealed that a sample size of 80 participants in each of the active study arms is required to detect a statistically significant difference with a power (1 – β) of .80. The sample size was further estimated based on a dropout rate of approximately 25%. We finally decided to randomize 100 participants to each of the conditions (3 arms, 100 per arm; CAU, Res-Up!, and REMOTION). The second goal of the study is exploratory, and thus no assumptions about differential effects can be made.

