## Results

Participant recruitment and data collection started in April 2020 and completed in July 2022. Results for the study are expected in 2023. Regarding our research questions, we expect participants of our study to benefit more from the interventions than participants in the CAU control on the dimensions of resilience and emotion regulation, respectively. To accomplish the initial status of resilience and emotion-regulation competencies, they will be assessed and related to intervention effects in the intervention groups. Furthermore, we expect to find possible differences between CAP and COMP when the intervention is delivered via a web platform.

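### Read as a within-arm analysis, the exploratory moderator question is biased towards compensation by regression to the mean; it should be tested against CAU.

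*Protocol article*

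**What the plan says.** The Protocol article describes two ways to study capitalization versus compensation. One compares the two programmes. The other, in the section on basic orientations in psychotherapy, looks at who benefits: "Another possible conceptualization is via the interaction of intervention focus with patient variables". The rule for interpreting it is then given for a single programme. When people who start with few adaptive skills gain most from the emotion-regulation programme, the article concludes that "this points to a compensation change process". The opposite pattern, with high scorers benefiting most, is taken as capitalization.

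The Aims section says how this will be explored: "the initial status of resilience and emotion-regulation competencies will be assessed and related to intervention effects in the intervention groups". The Results section repeats the restriction: "they will be assessed and related to intervention effects in the intervention groups". The first goal, in the same Aims section, is explicitly a comparison with CAU; the moderator sentence does not mention CAU. Planned Analysis specifies linear mixed models for the primary and secondary outcomes and within-group effect sizes from baseline to follow-up, but no moderator term.

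CAU contributes the data that a comparison would need: "Assessments will be made at baseline, 6 weeks (post), and 12 weeks (follow-up) for all participants".

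**The concern.** Inside one arm, an intervention effect at a given baseline level can only be observed as change. Baseline is one component of change, so people who score low by chance at baseline tend to score higher later, whether or not the programme does anything. That is the pattern the article labels compensation. The bias runs one way: it adds to a true compensation pattern and masks a true capitalization pattern. Only the difference between the programme slope and the CAU slope tells whether the programme's effect depends on baseline skill.

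At stake is the second of the article's two routes to its capitalization-versus-compensation question. A statement that either programme works by compensation could rest on an artefact.

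**Working it through.** **Arm size.** The article gives no figure for the moderator analysis, so the only figure to reproduce is the arm size. Sample Size Calculation says "We aim to detect small effect sizes of Cohen *d*=0.20" "regarding the Time×Group interaction for the 2 active conditions at an error level of .05", with power .80 and 80 per active arm; 100 are randomized to allow for about 25% dropout.

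- Take f = d/2 = 0.10, two groups and three measurements, and assume a correlation of 0.5 between measurements and sphericity (neither is stated).
- The noncentrality is f² × N × m/(1 − ρ) = 0.01 × 160 × 3/0.5 = 9.6 on 2 and 316 degrees of freedom. Power is 0.794.
- Power of .80 needs 82 per arm, so the stated 80 is reproduced within rounding.
- With 25% loss, 100 × 0.75 = 75 remain. The checks below use 75 to 80 per arm.

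**Same scale as moderator and outcome.** Let r be the correlation between baseline B and follow-up Y without treatment, with equal variances. The slope of change on baseline is r − 1, and

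corr(B, Y − B) = (r − 1)/√(2 − 2r) = −√((1 − r)/2).

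The article gives no r. It reports internal consistencies of .81–.90 and .90 for two of the scales, which are not retest correlations, so r = .6 to .9 is an assumption. In 4,000 simulated trials per setting, with a uniform treatment effect and no true moderation, the share with p < .05 was:

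| r | slope in one arm | correlation | one arm, n = 80 | interaction with CAU, 80 per arm |
|---|---|---|---|---|
| .6 | −0.40 | −0.45 | 98.6% | 4.9% |
| .7 | −0.30 | −0.39 | 95.1% | 5.3% |
| .8 | −0.20 | −0.32 | 81.2% | 5.2% |
| .9 | −0.10 | −0.22 | 51.5% | 5.7% |

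A separate simulation with 75 per arm gave 98.5%, 93.3% and 79.8% at r = .6, .7 and .8. As a check by Fisher's z at r = .7 and n = 80: atanh(0.387) × √77 = 3.58, and Φ(3.58 − 1.96) ≈ 0.95.

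Masking follows from the same slope. At r = .7, a true capitalization slope of +0.30 would show as −0.30 + 0.30 = 0.

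**BSI-18 as outcome.** Here the moderator M (skill or resilience) is not part of the change score. The artefact arises only if M and BSI-18 share temporary fluctuations at baseline. Every correlation below is an assumption.

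- Trait correlation −.5, r = .7 or .8, n = 80. The within-arm slope of BSI-18 benefit on M is (1 − r) × the correlation of the fluctuations. The false-positive rate is about 5% if that correlation is 0, 14% to 17% if it is −.3, and 29% to 40% if it is −.5.
- Baseline correlation −.5, shrinking to 60% or 70% of that at follow-up, BSI-18 r = .6, n = 75. The correlation of M with benefit is (−.50 + .30)/√0.8 = −.22, or (−.50 + .35)/√0.8 = −.17. The rate is about 48% or 30%.
- In that second setting, adjust for baseline BSI-18. The residual association is −.30 − (.6)(−.5) = 0 at 60%. At 70% it is −.35 + .30 = −.05, which is the capitalization direction.

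For BSI-18 the range is therefore about 5% to 48% with change scores, and baseline adjustment can remove or even reverse the artefact.

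**The case against.** The strongest reply is that the article never says CAU is excluded. The moderator sentence refers back to the effectiveness of the two programmes, and the first goal measures effectiveness against CAU, so intervention effects could mean contrasts with CAU. The article also speaks of an interaction with intervention focus. If moderator slopes were compared between Res-Up! and REMOTION, regression to the mean would cancel; in the same simulations that contrast was significant in about 5% of trials. This stands as far as it goes: exclusion of CAU is inferred from the wording. But no section states either contrast. Comparing the two programmes would also not show whether either one works by compensation, which is what the article's rule is about.

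A second reply is that the details of an exploratory model belong in the analysis plan, which is not shown. That holds for the model terms. The comparison set and the rule of interpretation, however, are written here, and an analysis plan that followed them literally would inherit the problem.

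A reader might infer that the analysis would return compensation almost regardless of the truth, for both programmes. The documents do not support that. The high rates need the same scale on both sides and change scores, and the article does not fix the outcome for this analysis. With BSI-18 the artefact may be small or absent.

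**Conclusion.** The concern holds in a limited form. As worded, the plan most naturally leads to a within-arm analysis, and under the article's own rule such an analysis is biased towards compensation. With the same scale, change scores and r from .9 down to .6, about 50% to 99% of trials without true moderation would show a significant slope. With BSI-18 the figure is about 5% to 48% on correlations not found in the article, and it can disappear with baseline adjustment. The interaction with CAU holds its error near 5% in every setting simulated.

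The article presents this analysis as something to be explored and calls the second goal exploratory. The comparison of each programme with CAU, the primary outcome analysis and the sample size do not depend on it. This should be fixed before the moderator results are interpreted; it does not threaten the trial's main conclusion.

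**What to change.** State that the moderator analysis uses all three arms in one mixed model and tests baseline moderator × group × time, with CAU as the reference for each programme and Res-Up! versus REMOTION as a further contrast. Name the outcome for each moderator. Base any statement about capitalization or compensation on that interaction with its confidence interval, not on a baseline–change association inside an arm.

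The cost is wording and additional interaction terms. CAU participants are assessed at the same three time points, so no data collection changes. The interaction will have a wider confidence interval than a within-arm slope, and with 75 to 80 per arm it may be inconclusive; the report should then say so.

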## Methods

### Study Design

The study is a multicenter 3-arm randomized controlled trial in which a CAU approach will be compared with 2 different web-based intervention programs (CAP: Res-Up! and COMP: REMOTION), which will be administered as an add-on to CAU.

Participants in the intervention groups will be given access to Res-Up! and REMOTION immediately, whereas participants in the CAU group will receive access to one of the interventions after 12 weeks (participants in the CAU group can choose which intervention they want to access). Assessments will be made at baseline, 6 weeks (post), and 12 weeks (follow-up) for all participants. Assessments at 6 and 12 weeks will be made irrespective of whether the participant is in face-to-face treatment.

The multicenter trial will take place at the outpatient clinics of the Training Center for Psychological Psychotherapy OWL (Bielefeld, Germany), the Centers for Psychotherapy Dortmund and Muenster (all German Association of Behavioral Therapy—Deutsche Gesellschaft für Verhaltenstherapie [DGVT]), and the Center for Mental Health and Psychotherapy (Department of Psychology and Psychotherapy, University Witten/Herdecke).

Primary and secondary outcomes will be gathered via link to web-based self-report questionnaires based on Qualtrics software [44] at baseline and 6 and 12 weeks after baseline.

All participants will be required to give their informed consent before enrollment in the study. The written consent will be obtained by trained psychotherapists at the outpatient centers. Furthermore, all participants are given the option to contact a study member during the intervention (“guidance on demand”) either via email (REMOTION) or chat (Res-Up!) but are not actively contacted by the team (except for reminders to complete the interventions or questionnaires and a welcome message). Figure 1 displays the flow of patients through the study.

**Figure 1 figure1:**
[figure not shown]
Flow of participants. CAU: care as usual.

### Sample Size Calculation

Sample size was calculated with the software G*Power [45]. We aim to detect small effect sizes of Cohen *d*=0.20 regarding the Time×Group interaction for the 2 active conditions at an error level of .05. A power analysis revealed that a sample size of 80 participants in each of the active study arms is required to detect a statistically significant difference with a power (1 – β) of .80. The sample size was further estimated based on a dropout rate of approximately 25%. We finally decided to randomize 100 participants to each of the conditions (3 arms, 100 per arm; CAU, Res-Up!, and REMOTION). The second goal of the study is exploratory, and thus no assumptions about differential effects can be made.

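### The stated 80% power for Cohen d=0.20 with 80 per active arm does not hold on the usual meaning of d; 80 fits an interaction f of about 0.10, which for two groups is 0.40–0.49 SD

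*Protocol article*

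**What the plan says.** The Sample Size Calculation section of the protocol article gives these elements:

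- Software: "Sample size was calculated with the software G*Power".
- Target: "We aim to detect small effect sizes of Cohen *d*=0.20 regarding the Time×Group interaction for the 2 active conditions".
- Significance level: "at an error level of .05", with sidedness not given.
- Result: "a sample size of 80 participants in each of the active study arms is required to detect a statistically significant difference with a power" of .80.
- Randomized number: 100 in each of the three arms, after an allowance for about 25% dropout.

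The section does not name the G*Power routine, the number of groups or measurements entered, the correlation, or the conversion from d to the effect size that the routine takes. Under Study Design there are three assessments (baseline, 6 weeks, 12 weeks), and under Planned Analysis the outcomes are analysed with linear mixed-effect models.

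**The concern.** With two arms of 80, a standardized difference of 0.20 is normally far out of reach. Repeated measures help, but only a very high correlation between measurements would close the gap. G*Power's repeated-measures routines take Cohen's f, not d. Setting f=d/2 is correct for a two-group main effect but not for a Time×Group interaction, where the same f stands for a larger between-arm difference.

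The article uses d elsewhere as an ordinary standardized effect: the Resilience section of the Introduction calls 0.41 small and 0.51–0.55 medium, and Planned Analysis will report Cohen d for change. A reader will put the 0.20 on the same scale. At stake is how a non-significant result is read, above all between the two programmes, which is the comparison the power sentence appears to address.

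**Working it through.** **Inputs.** From the article: d=0.20, alpha .05, power .80, 80 per arm (160 in two arms), three measurements. Assumed, because not stated: a two-sided test, equal correlation r between measurements (range .3–.7), equal SDs, no nonsphericity correction.

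**1. Reproducing the 80.** For the within-between interaction, noncentral F with λ = f²·N·m/(1−r), df1 = (k−1)(m−1), df2 = (N−k)(m−1), and f = d/2 = 0.10:

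- k=2 groups, m=3 times, r=.5, N=160: λ = 0.01×160×3/0.5 = 9.6, df 2 and 316, power .794. At N=164 (82 per arm) it is .805.
- k=2, m=2, r=.6, N=160: λ = 0.01×160×2/0.4 = 8.0, df 1 and 158, power .803.
- Three-group inputs also come close: k=3, m=2, r=.5 needs N=244, and k=3, m=3, r=.4 needs N=242 (about 81–82 per arm in each case).

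So 80 is reproducible with f=0.10 under several settings, and the article does not show which was used. A plain two-sample test with d=0.20 does not reproduce it: it needs 394 per arm two-sided.

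**2. What f=0.10 means for two groups.** Here f is the SD of the interaction cell effects in outcome-SD units. For a between-arm difference in change D:

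- Two times: cell effects are ±D/4, so f = 0.25·D and D = 0.10/0.25 = 0.40 SD.
- Three times, full difference at both weeks 6 and 12: f = ½·√[(4/9+1/9+1/9)/3]·D = 0.2357·D, so D = 0.42 SD.
- Three times, difference growing linearly to week 12: f = ½·√[(0.25+0+0.25)/3]·D = 0.2041·D, so D = 0.49 SD.

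**3. Power if the true difference in change is 0.20 SD, 80 per arm.** Two-sample noncentral t with noncentrality (0.20/s)·√(80/2). The SD s is √[2(1−r)] for a change score, √(1−r²) for a baseline-adjusted single time point, and √[(1+r)/2 − r²] for the baseline-adjusted mean of both post-baseline measures.

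| r | Change score | Baseline-adjusted, one time | Baseline-adjusted, mean of two |
|---|---|---|---|
| .3 | 0.19 | 0.26 | 0.39 |
| .5 | 0.24 | 0.31 | 0.43 |
| .7 | 0.37 | 0.42 | 0.55 |
| .8 | 0.51 | 0.55 | 0.69 |

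Power of .80 needs r of about .90, .89 and .85 respectively. At r=.5 the number needed per arm is 394 (change score) or 296 (baseline-adjusted, one time). The three-time interaction F test with D=0.20 gives 0.18–0.37 (step pattern) or 0.15–0.29 (linear pattern) for r=.3–.7.

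**4. Difference detectable with 80% power, 80 per arm.**

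| r | Change score | Baseline-adjusted, one time | Baseline-adjusted, mean of two |
|---|---|---|---|
| .3 | 0.53 | 0.42 | 0.33 |
| .5 | 0.45 | 0.39 | 0.31 |
| .7 | 0.34 | 0.32 | 0.27 |

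Across r=.3–.7 this is 0.32–0.53 SD for a single time point and 0.27–0.33 SD with both post-baseline measures.

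**The case against.** The strongest reply is that 80 is not a miscalculation. G*Power returns it, within rounding, for an interaction f of 0.10; the article attaches its d to the interaction, and d=2f is a familiar if loose shorthand. That stands as an account of where the number may come from, and it rules out calling the 80 an arithmetic slip. It does not rescue the sentence, which gives the effect as Cohen d=0.20 and never mentions f.

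A second reply is that the planned mixed model uses all three assessments, so single-time-point figures are pessimistic. This is partly right, and the more favourable figures are shown above; they still stop at 0.55 for r=.7 and 0.69 for r=.8.

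A third is that an article need not print every software input. Agreed: the missing routine and correlation are not the fault here. The fault is a stated combination of d, n, alpha and power that does not hold together.

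Stronger readings are tempting, but the document does not support them:

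- That f=0.10 was certainly entered. No routine, f or correlation is stated, and two-group and three-group inputs both land near 80.
- That the design detects exactly 0.40–0.49 SD. That is a two-group translation of f=0.10; the detectable difference depends on the correlation and the analysis.
- That a null result will be misused, including against care as usual. The power sentence refers only to the two active conditions, the section calls the second goal exploratory, and nowhere is 0.20 made an equivalence or relevance margin.

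**Conclusion.** The claim of .80 power for Cohen d=0.20 with 80 per active arm is wrong as written. The effect size is mislabelled; the software output itself need not be faulty. If the 80 came from a two-group run with f=0.10, the label understates the between-arm difference in change by a factor of about 2 to 2.5 (0.40/0.20 to 0.49/0.20). Whatever was entered, 0.20 SD does not reach 80% power at any assumed correlation from .3 to .8 in any analysis tried.

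The conclusion rests on reading d as a standardized between-arm difference in change and on the assumptions listed with the check. It does not touch the randomization, the primary outcome or the planned model.

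**What to change.** In the Sample Size Calculation section:

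- Keep 100 per arm and delete the claim of 80% power for d=0.20.
- Restate the sensitivity, from the inputs actually used, as the detectable between-arm difference in BSI-18 change, with the assumed correlation beside it. Only the authors can supply those inputs, so f=0.10 should not be printed unless it was what they entered.
- As a guide for what the restated figure should look like, use the ranges in step 4 of the check.
- Read non-significant results for the comparison between programmes against the restated figure.

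The cost is one reworded paragraph and a less favourable stated sensitivity. No participants are added and nothing in the conduct or analysis changes, which suits a trial whose Results section reports recruitment and data collection as complete.

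### At the plan's own 25% dropout, 100 per arm leaves 75 completers, 5 short of the 80 it requires in each active arm (minor)

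*Protocol article*

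**What the plan says.** Everything needed stands in one paragraph, Sample Size Calculation in the Methods of the protocol article. The effect is Cohen d = 0.20 "regarding the Time×Group interaction for the 2 active conditions", tested "at an error level of .05". The target power is .80, and for it the plan states that "a sample size of 80 participants in each of the active study arms is required to detect a statistically significant difference". On attrition it says: "The sample size was further estimated based on a dropout rate of approximately 25" per cent. The next sentence fixes the size: "We finally decided to randomize 100 participants to each of the conditions", with three arms.

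No inflation formula is given, and no reason for accepting fewer than 80 per active arm after dropout. The Discussion (Principal Findings) repeats the figure of 100 per arm, about 300 in all, so 100 is not a slip of the pen.

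**The concern.** A dropout allowance is meant to ensure that the required number remains after the expected loss. The required number is therefore divided by the retained fraction, 1 − 0.25. Here the number randomised falls short of that result. Anyone reading the paragraph will conclude that the trial can lose a quarter of its participants and still have power .80. On the paragraph's own figures it cannot.

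At stake is the accuracy of the sample-size justification, and a small amount of power for the comparison of the two active arms. The Limitations section itself names dropout as a known problem of web-based interventions, so the allowance is not a formality.

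**Working it through.** **Inputs from Sample Size Calculation:** 80 required per active arm; power .80; alpha .05; d = 0.20 for the Time×Group interaction; dropout about 25%; 100 randomised per arm.

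**Step 1. Can the 80 be reproduced?** The plan says: "Sample size was calculated with the software G*Power". It does not give f, the correlation between repeated measures, the nonsphericity correction, or the number of time points entered. The following are assumptions of this check: f = d/2 = 0.10, two groups, epsilon = 1. For the within-between interaction in a repeated-measures ANOVA, power comes from the noncentral F distribution with

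λ = f² × N × m / (1 − r), df1 = (k − 1)(m − 1), df2 = (N − k)(m − 1),

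where N is the total over both arms, m the number of measurements, r their correlation and k = 2 the number of groups.

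- m = 3 (Study Design: "Assessments will be made at baseline, 6 weeks (post), and 12 weeks (follow-up) for all participants"), r = .5: power .80 is reached at N = 163, or 81.5 per arm.
- m = 2, r = .6: power .80 is reached at N = 159, or 79.5 per arm.

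Both settings land close to 80, so the figure is plausible. Neither is shown to be the one the authors used.

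**Step 2. Dropout allowance.** This step needs no assumption beyond the printed figures.

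- Completers from 100 per arm: 100 × (1 − 0.25) = 75.
- Number needed to keep 80: 80 / (1 − 0.25) = 106.7, so 107. Check: 107 × 0.75 = 80.25.
- Dropout that 100 per arm can absorb: 1 − 80/100 = 20%.
- For comparison: 80 × 1.25 = 100 exactly.

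**Step 3. Shortfall.** 80 − 75 = 5 completers per active arm, or 10 across the two. In randomised participants, 107 − 100 = 7 per active arm, or 14 across the two.

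**Step 4. Power among completers, under the Step 1 assumptions.**

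| Setting | λ at 80 per arm (N = 160) | Power | λ at 75 per arm (N = 150) | Power |
|---|---|---|---|---|
| m = 3, r = .5 | 0.01 × 160 × 3 / 0.5 = 9.6 | .794 | 0.01 × 150 × 3 / 0.5 = 9.0 | .766 |
| m = 2, r = .6 | 0.01 × 160 × 2 / 0.4 = 8.0 | .803 | 0.01 × 150 × 2 / 0.4 = 7.5 | .777 |

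A cross-check that avoids the choice of m and r takes power as exactly .80 at 80 per arm and scales by the square root of n. With the normal approximation, Φ[(1.960 + 0.842) × √(75/80) − 1.960] = .774. All three routes put the loss at about 3 points.

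**The case against.** The strongest reply is that completers are not the analysed sample. The Planned Analysis section includes all randomised patients in linear mixed models, which use incomplete records without exclusion or imputation. Randomisation follows the baseline questionnaire (Recruitment and Randomization), so everyone randomised has a baseline value, and some who drop out will also have a 6-week value. The information per arm therefore lies somewhere between 75 and 100 complete cases, and partial data worth about 5 complete cases per arm would close the gap. This stands as a reason to expect a loss smaller than 3 points. It does not show that 80 is reached: the timing of dropout is not given, and a participant with baseline alone adds little to a Time×Group test. Nor does it remove the inconsistency, because the plan sets 80 as the requirement and then makes an allowance for dropout without saying that it counts on partial data.

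A second reply is that the rate is only approximate and that 100 reads as a rounded, pragmatic choice. But any rate above 20% leaves fewer than 80, and no pragmatic reason is stated.

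A third possible defence is that Planned Analysis defines dropouts as those without a baseline measurement. That cannot describe losses among the 100 randomised, since baseline comes before randomisation.

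Three stronger readings are tempting, and the document does not support them:

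- **That the authors inflated by multiplying by 1.25.** The exact match with 100 suggests it, but no formula is printed. The shortfall exists however 100 was reached.
- **That the trial is 15 completers short, or needed 321 participants.** The requirement of 80 is stated for the two active arms only. The figure of 321 (3 × 107) follows only if all three arms are kept equal.
- **That .766 or .777 is the power on the plan's own basis.** Those figures rest on inputs the plan does not state.

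**Conclusion.** The inconsistency is certain, because it follows from three printed figures: 80 required, about 25% dropout and 100 randomised cannot all hold. Its size is 5 completers per active arm, 10 across the two active arms.

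The effect on power is modest and less certain. It is about 3 points in a completer calculation, from about .79-.80 to about .77-.78, given f = 0.10 and the assumed correlations and time points, and probably less under the planned mixed model. A reader might infer that the trial is materially underpowered on this account, or that its validity is in doubt. Neither follows: the analysis model, the type I error and the risk of bias are untouched. This is a minor correction to the sample-size statement.

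**What to change.** Keep 100 per arm. The Results section of the article reports recruitment as completed in July 2022, so no further enrolment is asked for. Correct the dropout sentence to say that:

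- 25% dropout leaves about 75 completers per arm;
- 100 per arm retains 80 only if dropout is 20% or less;
- power at 75 per active arm is slightly below .80, with the value recomputed by the sponsor from its actual G*Power inputs.

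The values near .77 above are illustrations and should not be copied in as the planning figure. The sponsor may add that the mixed model also uses partial data from participants who drop out. The cost is a sentence or two and one rerun of the original calculation; the stated power becomes slightly lower.
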